## Methods: participants, interventions and outcomes

### Study setting {9}

The Mexican Institute of Social Security (IMSS) will be responsible for both the research centres where the trial will be carried out, as well as for the selection of the researchers that will participate in the trial.

The study will be carried out at the Infectious Disease National Medical Centre “La RAZA” Hospital. Participants will be recruited among health workers, their household members and patients that are diagnosed at La Raza or any of the outpatient clinics in its service area (north section of Mexico City and its suburbs).

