### Recruitment {15}

The trial will be advertised at each site and the participant identification centre and health workers provided with the trial team’s contact details. Occupational Health teams at each participating centre will be provided with the trial information which they can provide to health workers who consult them. Potential participants will also be approached after research on databases. 120 participants will be recruited in total (60 participants in each arm) over an overall period of 6 months.

Should recruitment targets be slower than anticipated other clinics, hospitals, and diagnostic laboratories in México City and its suburban area will be approached to enroll participants, which will be done centrally by the trial team in any case.

Recruitment will be monitored regularly to identify any barriers to recruitment. Reporting will be conducted on a regular basis over the trial set-up and recruitment period to the Trial Management Group (TMG), and trial oversight committees. Remedial action will be put in place as soon as any concerns have been raised.

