## Assignment of interventions: allocation

### Sequence generation {16a}

Participants will be randomised 1:1 using a stratification process, with the following factors: study site, age (≤ 55 vs > 55 years old), gender, obesity (BMI <30 vs ≥30), symptomatic or asymptomatic, current smoking status (Yes = current smoker, No = ex-smoker, never smoker), and the presence or absence of comorbidity (defined as diabetes, hypertension, ischaemic heart disease (including previous myocardial infarction), other heart diseases (arrhythmia and valvular heart disease), asthma, COPD, other chronic respiratory diseases) and, if the participant has or not been vaccinated. These data will be collected at the pre-screening telephone contact and will be used for the purposes of registration and IMP kit pre-allocation.

Considering the importance of starting therapy immediately upon entering this trial, IMP kit codes will be pre-allocated to the participants ahead of the screening/baseline visit on day 1.

The Trial Pharmacologist at CINVESTAV will generate a sequence of unique identifiers for every active/placebo IMP kit. A copy of the sequence will be held securely at UCL and at CINVESTAV.

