### Data management {19}

Data will be entered onto paper Case Report Forms (CRFs) or directly onto the RedCap database. Staff will receive training on data collection. Paper CRFs will be placed in clear plastic wallets which allow reading both sides of the CRF without opening the wallets. The plastic wallets will be decontaminated before leaving the participant's residence as per infection control guidance.

Identification logs, screening and enrolment logs will be kept at the trial site in a locked cabinet within a secured room.

Research team members across all participating sites will receive training on the FANTAZE protocol and on the data entry in the approved FANTAZE database.

All data will be handled in accordance with the Federal Law on Protection of Personal Data Held by Individuals 2010, the Data Protection Act 2018 and the GDPR 2016/679 including all further updates.

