## Statistical methods

### Statistical methods for primary and secondary outcomes {20a}

Summary of baseline characteristics, by trial arms, will be by frequency and percentage for categorical variables, and for continuous variables by mean and standard deviation (or median and inter-quartile range for non-normally distributed data).

The primary endpoint will be analysed using a linear mixed-effect model, including the main effects (each experimental treatment) as factors, and the interaction between them. Baseline values of viral load will be included for each subject and, linked within subjects using random intercept terms.

An analysis of covariance (ANCOVA) will also be performed: the ANCOVA model will use the viral load on Day 5 as the dependent variable and include the baseline value as independent variable.

Secondary endpoints include binary endpoints and continuous endpoints (note that the pharmacokinetic analysis of favipiravir and nitazoxanide is described in a separate section below).

For binary endpoints, a logistic regression will be used. The adjustment strategy will be the same as the primary endpoint.

The comparison of duration of fever following commencement of medication between trial arms will be by t-test, or non-parametric equivalent depending on the distribution of the data. Regression models will also be used to perform analyses adjusted for site (as random effect.).

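### None of the seven patient-level stratification factors enters a listed outcome model, and the only extra adjustment is a site random effect although the number of sites is unclear

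*Protocol article*

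**What the plan says.** **Allocation.** Sequence generation {16a} states: "Participants will be randomised 1:1 using a stratification process", "with the following factors: study site, age", followed by gender, obesity, symptom status, smoking, comorbidity and vaccination. That is eight factors, seven of them at patient level. Implementation {16c} lists six, without site and comorbidity. The abstract's Methods also lists six, without site and age.

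**Outcome models.** In Statistical methods {20a}, the primary mixed model has treatment terms, baseline viral load and a subject random intercept. The ANCOVA regresses the day 5 value with the baseline value as its covariate. The binary outcomes follow suit: "For binary endpoints, a logistic regression will be used. The adjustment strategy will be the same as the primary endpoint". Duration of fever is compared by t-test or a non-parametric equivalent, and the paragraph ends: "Regression models will also be used to perform analyses adjusted for site (as random effect". It does not say which other endpoints, if any, this covers.

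**Sites.** Study setting {9} says "The study will be carried out at the Infectious Disease National Medical Centre" and names one hospital, with outpatient clinics as places of diagnosis. The same section refers to "both the research centres where the trial will be carried out", and Data management {19} to "Research team members across all participating sites". Implementation {16c} and Recruitment {15} also use the plural. Recruitment adds a contingency, "Should recruitment targets be slower than anticipated other clinics, hospitals, and diagnostic laboratories", with enrolment still done centrally by the trial team.

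**The concern.** Two parts of the plan do not fit together.

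First, a trial that stratifies its allocation normally carries the stratification factors into the analysis. Stratified allocation makes the arms more alike on those factors than simple randomisation would. A model that ignores them still counts their contribution as noise, so its standard error is somewhat too large and any residual chance imbalance stays uncorrected. What is at stake is precision on the day 5 viral load comparison with about 54 evaluable participants per arm.

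Second, the one adjustment named beyond baseline viral load is for site, as a random effect. That term needs several sites to mean anything, and the article does not settle how many there are.

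**Working it through.** **1. The plan's own figure.** 108 / (1 − 0.10) = 120, as stated. The 108 cannot be reproduced, because alpha, power and SD are not given. With 54 per arm, a 1 log10 difference and an assumed two-sided 5% test, power is 80% at SD 1.85 and 90% at SD 1.60.

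**2. Strata.** Seven binary factors give 2^7 = 128 cells per site; the six-factor lists give 2^6 = 64. Under assumed prevalences of 0.20 to 0.85, 120 participants fill about 52 of the 128 cells, and about 26 of those hold one person. Balance on the factors is therefore only partial.

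**3. Effect of omitting the factors.** Simulation with N = 108, seven binary factors with equal contributions, permuted blocks of 4 within the 128 cells (block size assumed) and 3,000 runs per setting. Residual SD after baseline adjustment is 1.86 (assumed), so the standardised difference is 1/1.86. R² is the share of that residual variance explained by the seven factors (assumed).

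| R² | Type I error, without / with factors | Power, without / with factors |
|---|---|---|
| 0.05 | 5.0% / 5.6% | 78.4% / 78.6% |
| 0.10 | 4.4% / 4.9% | 80.2% / 82.2% |
| 0.20 | 4.2% / 5.4% | 80.6% / 86.7% |
| 0.30 | 3.7% / 4.8% | 80.9% / 90.4% |

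Power forgone is about 0, 2, 6 and 10 points. The Monte Carlo standard error of a 5% rate is √(0.05 × 0.95 / 3000) = 0.4 points, so the type I error result is clear at R² 0.30 and weak at 0.10. At R² 0.30, on the unit-variance scale, the unadjusted model reported an average standard error of 0.192, while its estimates actually varied with SD 0.180; the adjusted standard error was 0.164.

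**4. Cost of adjusting.** Intercept, treatment and baseline leave 108 − 3 = 105 residual degrees of freedom; seven more terms leave 98. Taking the variance of the adjusted estimate as (1 − R²) × 105/98 of the unadjusted one, break-even is R² = 7/105 = 6.7%. This is conservative, because stratification limits the imbalance that the adjustment has to pay for.

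**5. Sensitivity to the SD**, with the same degrees-of-freedom cost:

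| SD | Power without factors | With, R² 0.10 | With, R² 0.20 | With, R² 0.30 |
|---|---|---|---|---|
| 1.5 | 93.4% | 94.2% | 96.3% | 97.9% |
| 2.0 | 73.8% | 75.4% | 80.1% | 85.1% |
| 2.5 | 54.7% | 56.2% | 61.2% | 67.0% |

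**6. Site term.** With one site, the random effect adds the same constant to everyone and cannot be separated from the intercept. On a simulated dataset of 54 per arm, the REML log-likelihood was −46.169264 at site variances 0, 0.5, 1, 5 and 50. The treatment estimate did not move, and its standard error stayed at √(1/54 + 1/54) = 0.19245. With two or three sites the variance rests on one or two degrees of freedom.

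**7. Rare outcomes.** With 60 per arm and an assumed 1% risk, the chance that at least one arm has no event is 1 − (1 − 0.99^60)² = 0.79; at 2% it is 0.51. Admission, ICU and death may not support a multi-covariate logistic model.

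**The case against.** The strongest reply is that this is a condensed article and a covariate list is usual SAP content. The primary model is described as including certain terms, which does not exclude others. This stands in part: if the SAP already carries the factors, only alignment is needed. But the article does not leave adjustment open. It names the covariate and extends the same strategy to the binary outcomes.

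Four stronger readings are tempting, and the document does not support them:

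- *The trial has one centre, so a non-estimable term is specified.* Study setting names one hospital, but the same section and four others point to several centres or sites. What is shown is an inconsistent site structure. Even with one site the term is empty and changes neither the estimate nor its standard error.
- *No model contains any allocation factor.* Study site is a factor in {16a}, and {20a} adjusts for it. The statement is true of the seven patient-level factors.
- *The adjusted analyses as a whole depend on site.* The sentence is a supplementary line in the fever paragraph; the primary model and the ANCOVA name no site term.
- *Precision is lost that would cost nothing to recover.* The gain depends on an R² that the article does not give, and below about 6.7% adjustment may not pay.

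It is also fair to say that standard errors that are too large and strata too sparse to balance cannot both apply in full. The simulation contains both and shows the net effect to be mild.

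**Conclusion.** The point holds as one of efficiency and consistency. The seven patient-level factors used for allocation are in none of the models listed for the primary and secondary outcomes. The resulting inference on the primary endpoint is valid but mildly conservative: simulated type I error about 4.4% to 3.7%, and about 2 to 10 points of power forgone, at R² 0.10 to 0.30. Near R² 0.05 the loss is negligible. There is no bias. These sizes rest on assumed SD, R², prevalences and block size.

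The site random effect cannot be judged until the number of sites is stated. It is empty with one site and very poorly estimated with two or three, so on either reading it needs changing.

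**What to change.** 1. Reconcile the factor lists in the abstract, Sequence generation {16a} and Implementation {16c}, and state the number of sites. The rest depends on this.
2. Add the reconciled patient-level factors as fixed main effects beside baseline viral load in the primary mixed model, the ANCOVA and the regressions for non-rare secondary outcomes.
3. Drop the site random effect if there is one site; use a fixed effect if there are a few. Say which endpoints the site adjustment covers.
4. For admission, ICU and death, keep adjustment minimal.
5. Optionally add days since symptom onset as a prognostic covariate. Symptom status is already a stratification factor, so no second asymptomatic indicator is needed.

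Cost: analysis wording only, since {16a} has the factors collected at the pre-screening call. Adjustment uses about seven degrees of freedom out of 108 and may not pay if the factors explain less than about 6.7% of residual variance. In the logistic models the adjusted odds ratio is conditional on the covariates and differs from the unadjusted one, so the report should say which is given.

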### Interim analyses {21b}

There will be no interim analyses. Monitoring of the safety of the trial will be undertaken by the IDMC which will have untrammeled access to the trial data, and whose work is governed by a separate charter.

### Methods for additional analyses (e.g. subgroup analyses) {20b}

#### Pharmacometric analysis plan

Population PKPD modelling and dosing simulations will be undertaken with non-linear mixed-effects modelling. Viral load with time will be modelled with a viral dynamic model, and the influence of favipiravir and nitazoxanide included to estimate an in vivo EC50.

Plasma concentrations will be sent from the bioanalytical laboratory on a spreadsheet and dosing history and relevant covariate information extracted from the clinical database. These data will be imported into R (version 3.4 or above) and merged for exploratory analysis and formatted for subsequent modelling using NONMEM version 7.4 or above (Globomax, USA) and or nlmixr version 1.0 of above.

Model selection criteria will include (i) successful stratification, (ii) standard error of estimates, (iii) number of significant digits, (iv) termination of the covariance step and (v) correlation between model parameters. Goodness of fit will be assessed by graphical methods, including population and individual predicted vs. observed concentrations, conditional weighted residuals vs. observed concentrations and time, correlation matrix for fixed vs. random effects, correlation matrix between parameters and covariates and normalised predictive distribution error (NPDE). Comparison of hierarchical models will be based on the likelihood ratio test. A superior model will be also expected to reduce inter-subject variance terms and/or residual error terms. Standard error of the parameter estimates will be approximated using of the asymptotic covariance matrix.

#### Additional analyses

Viral sequencing will be undertaken according to established protocols and analysis of mutagenesis, or the appearance of potentially deleterious mutations will be interrogated as previously described for other RNA viruses.

### Methods in analysis to handle protocol non-adherence and any statistical methods to handle missing data {20c}

The primary analysis will be on the intention-to-treat (ITT) population. There will be no imputation for missing data for any of the study outcomes.

A modified ITT analysis will be performed that will only include participants who have a confirmed diagnosis at baseline of SARS-CoV-2 infection (diagnostic swab and nose swab samples collected at Baseline).

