#### Participant inclusion criteria

Health workers, their household members and patients treated at IMSS facilities with the following:Symptoms compatible with COVID-19 disease (fever >37.8°C on at least one occasion and either cough and/ or anosmia) within the first 5 days of symptom onset (date/time of enrolment must be within the first 5 days of symptom onset).Or any symptoms compatible with COVID-19 disease (may include, but are not limited to fever, cough, shortness of breath, malaise, myalgia, headache, coryza) and tested positive for SARS-CoV-2 within the first 5 days of symptom onset (date/time of enrolment must be within the first 7 days of symptom onset).Or no symptoms but tested positive for SARS-CoV-2 within the last 48 h (date/time of test must be within 48 h of enrolment).2.Male or female aged 18 years to 70 years old inclusive at screening.3.Willing and able to take daily nose swab samples.4.Able to provide full informed consent and willing to comply with trial-related procedure.

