#### Screening/baseline visit (day 1)

A delegated site staff will visit the participants at their home. After they have been given sufficient time to ask questions and provided written consent, participants will undergo a final assessment for eligibility (including a urine pregnancy test for women of childbearing potential) and will be recruited to the trial. A baseline nose swab sample for virological analysis and baseline blood samples will be taken. A baseline diagnostic nose and throat swab will be taken if the participant has not been tested for COVID-19 yet.

If they are eligible, participants will be randomised and provided with a trial medication kit, symptoms diary, containers for daily nose swab samples collection, two stool collection containers, a thermometer and instructions for taking their medications, collecting samples and recording daily body temperature readings.

Participants will be considered fully randomised once they take their first trial medication dose, witnessed by the delegated site staff. Arrangements will be made for their next trial visits.

If participants are deemed ineligible following one of the above assessments, data will still be collected on all assessments listed above apart from swab, nose swab and bloods.

The reason(s) for ineligibility will be explained to participants and any questions they have will be answered. They will be thanked for their participation and any relevant information from this will be recorded on the CRF.

If participants are deemed ineligible following results from safety bloods collected at screening/baseline visit, a delegated site research staff will contact the participant (within 6 h of results receipt) to explain the reason(s) for ineligibility and instruct them to interrupt the therapy immediately. The research staff will enquire on any adverse reactions and side effects that the participant might have experienced since starting the trial medications and record details on the screening/baseline CRF. In order to ensure the participant’s safety, arrangements for immediate collection of the medication kit from the participant’s home will be made (within 24 h), and a pills count will be performed on receipt of the medication kit at site.

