### Sample size {14}

We have conducted extensive power calculation and power simulation exercises for the proposed design [6]. In the proposed design 120 participants (108 evaluable participants, which implies a 10% allowance for attrition and other methodological challenges) will be recruited, so that half of the participants receive both favipiravir/nitazoxanide treatment, and the other half receive favipiravir/nitazoxanide placebo treatment. We hypothesised that around a 1 log10 difference in viral load by day 5 would be clinically significant.

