Blood samples	• Full blood count (3mL) • Urea and electrolytes, liver function tests, uric acid (7mL) • Serum for storage (10mL) Plasma base line pharmacokinetic samples (1X2 mL)		• Full blood count (3mL) • Urea and electrolytes, liver function tests, uric acid (7mL) • Serum for storage (10mL) • Plasma Pharmacokinetic samples (3×2mL)	• Full blood count (3mL) • Urea and electrolytes, liver function tests, uric acid (7mL) • Serum for storage (10mL)
Nasopharyngeal swab (*only if COVID-19 testing not done yet)*	• Diagnostic sample			
Nose swab	Sample for viral load measurement/viral sequencing	Sample for viral load measurement/viral sequencing taken daily [self- sampled]	Sample for viral load measurement/viral sequencing	
Stool samples			Sample for viral load measurement/viral sequencing	Sample for viral load measurement/viral sequencing

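### Uninfected symptom-only entrants shrink the primary ITT viral-load difference, and the modified ITT meant to correct this asks for a baseline diagnostic swab that already-tested positives do not give

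*Protocol article*

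**What the plan says.** On the analysis population, section {20c} states: "The primary analysis will be on the intention-to-treat (ITT) population". It adds a modified ITT for participants with infection confirmed at baseline, and describes the confirmation as "diagnostic swab and nose swab samples collected at Baseline".

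The inclusion criteria give three entry routes. The first needs symptoms only, "fever >37.8°C on at least one occasion and either cough and/ or anosmia", with no test result. The second and third (other symptoms, or none) both require a positive SARS-CoV-2 test.

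Under Screening/baseline visit (day 1), "Participants will be considered fully randomised once they take their first trial medication dose", and that dose is taken during the same visit. On the diagnostic sample: "A baseline diagnostic nose and throat swab will be taken if the participant has not been tested for COVID-19 yet". Table 3 sets the same condition, "only if COVID-19 testing not done yet". The baseline nose swab for virology carries no such condition.

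Sample size {14} sets the benchmark: "We hypothesised that around a 1 log10 difference in viral load by day 5 would be clinically significant".

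**The concern.** Three things combine. People can enter on symptoms alone. Dosing does not wait for a PCR result; the baseline-visit section provides for stopping someone found ineligible on safety bloods, but nothing removes a participant whose swab proves negative. And ITT is primary. A participant without the virus sits at the assay floor at baseline and at Day 5 in both arms. That person adds nothing to the difference in viral load and counts as undetectable in both arms.

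The ITT estimate is therefore a mixture of the antiviral effect and zero, set against a benchmark that describes infected people. The analysis that should separate the two is the modified ITT. Its definition does not fit the sampling plan, because it names a swab that participants who entered on a positive test are not asked to give. At stake is whether a proof-of-principle trial reports a clean estimate of antiviral effect in any pre-specified population.

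**Working it through.** **The plan's own figure.** 108 evaluable with a 10% allowance: 108 / 0.90 = 120 recruited, 54 evaluable per arm. This reproduces. The 108 itself cannot be rebuilt, since the article gives no alpha, power or SD.

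**Dilution of the primary estimate.** Let f be the uninfected share (assumed) and Δ the difference in infected participants. Uninfected participants contribute zero, so the ITT difference is (1 − f)Δ. With Δ = 1.0 log10:

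| f (assumed) | ITT difference | Confirmed set |
|---|---|---|
| 10% | 0.90 | 1.00 |
| 20% | 0.80 | 1.00 |
| 30% | 0.70 | 1.00 |
| 40% | 0.60 | 1.00 |

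An ANCOVA simulation agreed to within about 0.01 log10 (108 participants, baseline mean 6 and SD 1.5 log10, correlation 0.5, uninfected held at the floor, 2000 runs per cell). Put the other way, at f = 20% the effect in infected people must be 1.0 / 0.8 = 1.25 log10 for ITT to show 1.0.

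**Power, continuous endpoint.** Both primary models in section {20a} use baseline viral load, which identifies most of the uninfected. If it absorbs them fully, the residual SD falls from σ to about σ√(1 − f). With n per arm the ITT signal is

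(1 − f)Δ / (σ√(1 − f)) × √(n/2) = (Δ/σ) × √(n(1 − f)/2),

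which is the signal in the confirmed set with n(1 − f) per arm. The simulation gave about 0.93 in both sets at f = 20%.

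**Undetectable at Day 5.** Assume 20% v 40% undetectable in infected participants and f = 20%.

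- ITT, first arm: 0.8 × 20% + 20% = 36%.
- ITT, second arm: 0.8 × 40% + 20% = 52%.
- The raw difference falls from 20 to 16 percentage points.

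Section {20a} plans logistic regression with the primary endpoint's adjustment. Simulated power with baseline adjustment (correlation 0.5 assumed):

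| f (assumed) | Confirmed set | ITT |
|---|---|---|
| 10% | 0.65 | 0.64 |
| 20% | 0.61 | 0.62 |
| 30% | 0.55 | 0.55 |

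**The modified ITT rule against the sampling plan.**

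| Entry route | Positive test required? | Baseline diagnostic swab | Baseline nose swab |
|---|---|---|---|
| Fever plus cough and/or anosmia | No | Yes, if not yet tested | Yes |
| Any compatible symptoms | Yes | No, already tested | Yes |
| No symptoms | Yes | No, already tested | Yes |

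If both swabs are needed, the second and third routes drop out. Asymptomatic participants can enter only by the third, so all of them go, and with them one level of a stratification factor.

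**The case against.** **ITT is legitimate and the confirmed analysis is already planned.** Including everyone treated on suspicion is a conservative choice for a trial that stresses starting at once. This stands in part: ITT as primary is not an error in itself. But the stated objective is a decrease in viral load, and the benchmark is meaningful only where there is virus. Infection status at baseline is fixed before dosing, so restricting on it keeps the randomised comparison.

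**The parenthesis may simply list the samples used.** Every participant gives a baseline nose swab, so an already-tested positive could be confirmed from that alone. Excluding people because they had tested positive is an unlikely intention. This also stands: an either-swab meaning is plausible. The text nevertheless joins the two with *and*, and the wording should be settled before unblinding.

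**A reader might infer a loss of power.** Unadjusted formulas suggest one. For the binary endpoint, power is 53% (43 per arm, 20% v 40%) against 39% (54 per arm, 36% v 52%). For the continuous endpoint at f = 20%, it is 71% in the confirmed set against 61% in ITT (SD 1.85, the value giving 80% power at 54 per arm with an assumed two-sided alpha of 0.05). Neither uses the planned analysis. Both models adjust for baseline viral load, and with that adjustment the loss disappears under the assumptions above. The documents do not support a power claim.

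**A qualifying prior positive test would not be a clean definition either.** The second route allows enrolment up to day 7 of symptoms, so some prior positives may be undetectable on Day 1 and dilute the result in the same way. This is right, and the fix takes account of it.

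**Conclusion.** The point holds as a matter of estimation and definition. The direction of the dilution is certain if any uninfected people are randomised. Its size is (1 − f), about 0.80 log10 instead of 1.0 at an assumed 20%, and the document gives no figure for f. The raw percentages undetectable are diluted too. Equal power in the two sets rests on uninfected participants sitting at the floor at both times and on the baseline-adjusted models being used as planned.

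The modified ITT conflict is a matter of text: read literally, the rule excludes entrants with a qualifying prior positive, including every asymptomatic one. A reader might conclude that the trial will certainly discard its best-confirmed participants. That goes too far, because the either-swab meaning is plausible. The definition needs correcting, and the 1 log10 benchmark needs to be tied to infected participants.

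**What to change.** Before unblinding:

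1. Define the confirmed-infection set as all randomised participants with a positive PCR on any pre-dose Day 1 sample, diagnostic swab or nose swab.
2. For both the Day 5 viral load and the undetectable-at-Day-5 endpoint, also require a detectable baseline nose-swab load.
3. Use this set as the primary viral-load population. If ITT stays primary, state that the 1 log10 benchmark is judged in the confirmed set.
4. Keep all randomised participants as the supporting ITT analysis and for safety.

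No new samples are needed, and with no interim analysis planned the change can still be made before unblinding. It does need a protocol amendment submitted to the committee, with recruitment already under way. The primary set also becomes smaller: at f = 20%, 108 × 0.8 ≈ 86 evaluable. That costs no material power relative to ITT in the same trial. Keeping 108 confirmed evaluable participants would take 108 / (0.9 × (1 − f)) recruits, that is 134, 150 or 172 at an assumed 10, 20 or 30%.
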